**Methods/design:**

An investigator-initiated, double-blind, randomized, sham-controlled, single-center trial will be conducted. Twenty mildly to moderately affected SCA3 patients (Scale for the Assessment and Rating of Ataxia score between 3 and 20) will be included and randomly assigned in a 1:1 ratio to either cerebellar anodal tDCS or sham cerebellar tDCS. Patients, investigators, and outcome assessors are unaware of treatment allocation. Cerebellar tDCS (20 min, 2 mA, ramp-up and down periods of 30 s each) will be delivered over ten sessions, distributed in two groups of five consecutive days with a two-day break in between. Outcomes are assessed after a single session of tDCS, after the tenth stimulation (T1), and after three, six, and twelve months. The primary outcome measure is the absolute change of the SARA score between baseline and T1. In addition, effects on a variety of other motor and neuropsychological functions in which the cerebellum is known to be involved will be evaluated using quantitative motor tests, static posturography, neurophysiological measurements, cognitive assessment, and questionnaires.

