## Methods/design

### Study design

The SCA3-tDCS study is an investigator-initiated, double-blind, randomized (1:1), sham-controlled, single-center trial that will take place at the Radboud University Medical Center, Nijmegen, the Netherlands. Cerebellar tDCS will be delivered during five consecutive days for two weeks, with a two-day break in between. Primary and secondary outcome measures (see Tables 1 and 2) are assessed at baseline (T0 before tDCS), after a single session of tDCS (T0 after tDCS), after the tenth session of tDCS (T1), and after three, six, and twelve months of follow-up (T2, T3, and T4, respectively). For this purpose, we will use a combined approach of a standardized neurological examination, quantitative motor tests, cognitive assessment, questionnaires, and neurophysiological measurements (Table 1). This combination of tests reflects the broad range of motor, cognitive, and affective functions the cerebellum is known to be involved in, and represents recognized domains of deficit in patients with cerebellar diseases.

**Table 1 Tab1:** Overview of the questionnaires, neurological tests, and kinetic and neurophysiological measurements at the various points in time of the SCA3-tDCS study

	T0 baseline	T0 after tDCS	T1 day 12	T2 3 months	T3 6 months	T4 12 months
Questionnaires						
EQ-5D-5L	X		X	X	X	X
PHQ-9	X		X	X	X	X
POMS 32-item	X		X	X	X	X
iMCQ	X					X
IPAQ parts 1 and 4	X			X		X
FARS part II (ADL)	X		X	X	X	X
Neurological examination						
CCAS scale	X		X	X	X	X
SARA	X	X	X	X	X	X
8MWT	X	X	X	X	X	X
9HPT	X	X	X	X	X	X
PATA repetition	X	X	X	X	X	X
INAS	X		X	X	X	X
Measurements						
TMS	X		X			
Delay EBC	X		X			
Static posturography	X	X	X			

*EQ-5D-5L* EuroQol 5-Dimension 5-Level, *PHQ-9* Patient Health Questionnaire-9, *POMS* Profile of Mood States, *iMCQ* Institute for Medical Technology Assessment (iMTA) Medical Consumption Questionnaire, *IPAQ* International Physical Activity Questionnaire; *FARS* Friedreich Ataxia Rating Scale, *ADL* Activities of Daily Living, *CCAS* Cerebellar Cognitive Affective Syndrome, *SARA* Scale for the Assessment and Rating of Ataxia, *8MWT* 8 m walk test, *9HPT* 9-hole peg test, *INAS* Inventory of Non-Ataxia Signs, *TMS* Transcranial magnetic stimulation, *EBC* Eyeblink conditioning

**Table 2 Tab2:** Outcome measures and tests

Outcome domain	Test	Time point
Primary outcome measure		
Cerebellar ataxia severity	SARA (absolute change from baseline)	T1
Secondary outcome measures		

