### Statistical analysis

Statistical analyses will be conducted using SPSS and, in general, the significance level is set at *p* < 0.05. Where appropriate, we will use either chi-square tests, t-tests, or two-way ANOVAs with TIME as within-subject factor (number of levels depending on the specific outcome measure, ranging from two to five) and TREATMENT as between-subject factor (anodal tDCS versus sham tDCS). Subsequently, Bonferroni-corrected post-hoc testing is performed to explore significant main effects. Possible correlations with functional scores will be addressed using Spearman’s rank-order correlations.

This study is exploratory in nature. In the previously conducted Benussi et al. trial, the authors included 20 patients with a variety of ataxias and were able to demonstrate significant differences between the stimulation and sham groups in SARA, ICARS, 8MWT, and 9HPT [29]. In the current study, the same sample size of 20 SCA3 patients is chosen (*n* = 10 real stimulation, n = 10 sham stimulation). Based on the data presented in the aforementioned study, a calculation (G*Power 3) revealed a power of 83% to detect significant differences when using SARA as the primary outcome measure (effect size 0.46, α = 0.05, sample size 20).

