## Discussion

n this randomized, double-blind, sham-controlled trial the effects of a two-week regimen with daily sessions of cerebellar anodal tDCS will be evaluated for the first time in SCA3 patients. Since patients with less severe ataxia tended to have the largest decrease in coordination deficits in a previous pilot study [29], which likely suggests that the volume of viable cerebellar cortex that can be stimulated plays a crucial role, we will include mildly to moderately affected individuals. Although it is the main aim of this trial to investigate the effects of cerebellar tDCS on ataxia severity, a variety of other outcome measures will be used that reflect the spectrum of deficits observed in patients with cerebellar diseases such as SCA3. In fact, ours is the first study in patients with ataxia that also examines the effects of cerebellar tDCS on non-motor parameters. Relating to the clinically-oriented nature of the study, the outcome measures are mainly administered at the outpatient clinic. In addition, a paired-pulse TMS paradigm will be applied to investigate whether the physiological phenomenon of cerebellar brain inhibition – known to be reduced or absent in patients with lesions in the cerebellar efferent pathway – returns after repeated tDCS sessions.

While the focus will be on the immediate post-treatment (T1) versus baseline differences, we plan to have a follow-up of up to one year. It is very important to determine the exact time curve of the effect (if any) in order to establish the repeat frequency of the intervention to design implementation protocols. Furthermore, we will investigate whether transient effects on motor outcomes are already elicited by a single session of tDCS. In this respect, the SARA score and performances on the 8MWT, 9HPT, PATA repetition rate, and static posturography at T0 will all be completed within 30 to 45 min after the end of the cerebellar tDCS, which falls well within the estimated time window of after-effects of a single tDCS bout [60].

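### For outcomes followed from T1 to T4, the multi-level within-subject ANOVA drops every patient who misses one visit, including that patient's valid T1 data

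*Protocol article*

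**What the plan says.** In the protocol article, Statistical analysis, the software is fixed ("Statistical analyses will be conducted using SPSS") and so is the menu of tests: "Where appropriate, we will use either chi-square tests, t-tests, or two-way ANOVAs with TIME as within-subject factor", the factor having a "number of levels depending on the specific outcome measure, ranging from two to five". Treatment is the between-subject factor. No outcome is assigned to a particular test.

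Under Study design, assessments take place at baseline, after one session, "after the tenth session of tDCS (T1), and after three, six, and twelve months of follow-up". Table 1 gives exactly five assessments (T0, T1, T2, T3, T4) for EQ-5D-5L, PHQ-9, POMS, FARS part II, the CCAS scale and INAS. SARA, the 8 m walk test, the 9-hole peg test and PATA have the same five plus one directly after the first session.

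The abstract defines the primary endpoint: "The primary outcome measure is the absolute change of the SARA score between baseline and T1". Table 2 lists SARA after the first session and at T2-T4 in a separate secondary row. The Discussion adds: "While the focus will be on the immediate post-treatment (T1) versus baseline differences, we plan to have a follow-up of up to one year".

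**The concern.** The upper limit of five levels matches the T0, T1-T4 schedule, so a five-level ANOVA is the natural reading for outcomes followed to month 12. A classical within-subject ANOVA needs a value at every level. A patient seen at baseline, T1, T2 and T3 but not at month 12 leaves the whole model, and the T1 contrast from that model then depends on who attended a year later.

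This bears on a question that the trial treats as important. The Background asks how long any benefit lasts, and the Discussion wants the time course in order to decide how often treatment would need repeating. That curve would come from the multi-visit model. With 10 patients per arm, each exclusion costs precision. If attendance is related to the outcome, the estimate at every visit can also shift.

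**Working it through.** **The plan's own figure.** The only related number is the power: 83% with effect size 0.46, α = 0.05 and N = 20. It cannot be tied to one test, because the effect-size metric, the number of levels and the within-patient correlation are not stated.

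- A two-sided two-group t-test on T0-T1 change gives 16.4% if 0.46 is Cohen's d, and 49.5% if it is Cohen's f (d = 2 × 0.46 = 0.92).
- A four-level interaction test with noncentrality f² × N × (m − 1) = 0.46² × 20 × 3 gives 83.4%, but nothing in the text selects that version.

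The loss is therefore expressed in patients, not in power.

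**Inputs.**
- N = 20, 10 per arm (Statistical analysis).
- Four post-baseline visits in the five-level model: T1, T2, T3, T4 (Study design, Table 1).
- Baseline observed in everyone (assumption).
- Probability q of missing any one visit, independent across visits: 2%, 5%, 10% (assumption; the documents give no rate. The section on intervention and study procedures allows withdrawal at any time).

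**Formulas.**
- Complete at all levels: 20 × (1 − q)⁴
- With T1 data: 20 × (1 − q)
- Valid T1 data dropped: the difference

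| q | Complete at all five levels | With T1 data | Valid T1 data dropped |
|---|---|---|---|
| 2% | 20 × 0.98⁴ = 18.4 | 19.6 | 1.2 |
| 5% | 20 × 0.95⁴ = 16.3 | 19.0 | 2.7 |
| 10% | 20 × 0.90⁴ = 13.1 | 18.0 | 4.9 |

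The right comparator is the number with T1 data, not 20: no method recovers a T1 value that was never recorded.

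**Sensitivity to independence.** With the same q, if the same patients miss all four visits, 20 × (1 − q) are complete and no valid T1 data are lost. If no patient misses more than one visit, 20 × (1 − 4q) are complete. At 5% that is 16, a loss of 19 − 16 = 3; at 10% it is 12, a loss of 18 − 12 = 6. So the range is 0 to 3 patients at 5% and 0 to 6 at 10%.

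**Which analyses are exposed.**
- Exposed if analysed over all visits: SARA, 8 m walk test, 9-hole peg test, PATA, INAS, EQ-5D-5L, PHQ-9, POMS, CCAS scale, FARS part II.
- Not exposed to missed T2-T4 visits: TMS and eyeblink conditioning (T0 and T1 only), posturography (T0 before and after stimulation, T1), and the proportion with a SARA decrease of at least 1.5 points at T1.
- Primary SARA change from T0 to T1: not exposed under a t-test on change or a two-level ANOVA; exposed if read from the five-level model.

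**The case against.** The strongest reply is that the primary endpoint is a two-time-point change, that the Discussion puts the focus on T1 against baseline, and that both t-tests and two-level ANOVAs are on the menu. This stands. A reader might infer that the primary result will lose patients because of visits missed months later. The text does not say so, and Table 2 keeps the T1 change apart from the later SARA scores. Equally, the text does not rule it out, because SARA at T1 is not assigned to a test.

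Four further points on that side:

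- **Six assessments, five levels.** A reader might see an inconsistency for SARA and the three timed motor tests. There is none: the single-session effect is a separate objective, so T0 plus T1-T4, with a separate before/after comparison, is a coherent plan.
- **Equal correlation over unequal gaps.** The univariate test needs sphericity, which is weaker than equal correlation and is not an issue with two levels. Standard corrections exist and may sit in a fuller document. This is secondary.
- **Missing-data rules belong in the analysis plan.** Agreed, and their absence here is not the point. The named method itself discards incomplete patients, and only imputation or a change of method alters that.
- **Selective attendance is unproven.** Also agreed. The eligibility section cites greater improvement in less affected patients, but nothing in the article links severity or perceived benefit to attendance. Bias is possible, not shown.

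The study also describes itself as exploratory, which lowers the stakes without making the choice efficient.

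**Conclusion.** The point holds for the ten outcomes followed over T1-T4 whenever they are analysed in a multi-level within-subject ANOVA: one missed visit removes all of a patient's data from that model. Under independent misses of 2%, 5% and 10% per visit, this costs about 1, 3 and 5 patients with valid T1 data out of 20. Those rates are assumptions, and if misses cluster in the same patients the loss is smaller, down to none. The conclusion takes the ANOVA in its usual SPSS repeated-measures form, without imputation.

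The documents do not support saying that the primary analysis will lose T1 data. They leave that open, which is a reason to close it. The change should be made: it is cheap, it stays within the named software, and it protects the time-course question.

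**What to change.** 1. State that the primary SARA comparison from T0 to T1 is analysed in all randomised patients with T1 data, independently of later attendance, or is taken as the T1 contrast from the mixed model below.
2. For T1-T4 outcomes, replace the multi-level ANOVA by a linear mixed model (SPSS MIXED, REML, small-sample degrees of freedom) with baseline, TREATMENT, TIME and TREATMENT × TIME as fixed effects. Use all observed visits and report the between-arm contrast at each visit.
3. Keep the assessment after the first session as its own comparison.

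The cost is wording and slightly more programming, with no new visits, data or patients. The covariance structure must be named in advance with a fallback suited to 20 patients: an unstructured matrix over four visits has 4 × 5 / 2 = 10 parameters and may not be estimable, and a simpler fallback such as compound symmetry brings back a correlation assumption. The mixed model also relies on data being missing at random, which should be stated.

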Cerebellar transcranial direct current stimulation (tDCS) is an increasingly used, safe, cheap, and non-invasive tool in neuroscience that is able to modulate cerebellar excitability [18, 19]. Computational modeling studies have demonstrated the biophysical feasibility of modulating cerebellar structures using tDCS with only negligible spreading effects to neighboring regions [20, 21]. Initially, this technique has been successfully applied in healthy volunteers to investigate the neural correlates of motor learning and cognitive and emotional processes [19, 22, 23]. More recently, studies also started to explore its therapeutic potential in a variety of neurological conditions [24, 25]. The first promising results of this technique in ataxia patients – significant reduction of upper limb postural and action tremor and dysmetria – have been described in single cases of SCA2 and ARCA3 due to *ANO10* gene mutations [26, 27]. These effects were subsequently corroborated on a larger scale by Benussi and colleagues in a randomized, double-blind, sham-controlled study enrolling a rather heterogeneous group of nineteen patients with both hereditary and acquired ataxias. Compared to the sham condition, a single session of anodal cerebellar tDCS resulted in a significant transient improvement in scores on the Scale for the Assessment and Rating of Ataxia (SARA), International Cooperative Ataxia Rating Scale (ICARS), 9-hole peg test (9HPT), and 8 m walk test (8MWT) [28]. Furthermore, a double-blind, randomized, sham-controlled trial by the same authors assessing the efficacy of tDCS five days per week for two consecutive weeks in a heterogeneous group of twenty ataxia patients – five SCA2, one SCA14, two SCA38, one Friedreich ataxia, one ataxia with oculomotor apraxia type 2, four multiple system atrophy cerebellar type, one fragile X-associated tremor/ataxia syndrome, and five sporadic adult-onset ataxia of unknown etiology – showed a significant improvement on all of the abovementioned scores up to three months after stimulation. This clinical amelioration was paralleled by restoration of the physiological inhibition of the pathways between the cerebellum and the contralateral motor cortex, as measured with double-coil transcranial magnetic stimulation (TMS) [29]. More specifically, this study was able to achieve a SARA score reduction of almost three points up to three months after stimulation, which would nearly equal the progression in SCA3 over two years [30]. Recently, these authors published the results of another randomized, double-blind, sham-controlled trial in twenty ataxia patients with mixed etiologies and found similar results regarding symptomatic ataxia improvement and return of cerebellar brain inhibition after ten sessions of cerebello-spinal tDCS [31]. No serious adverse events of cerebellar tDCS have been reported in these and other studies and it is therefore considered a safe and tolerable method. Possible side effects mainly include a transient itching, tingling, or mild burning sensation underneath the electrodes.

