### Objectives

The primary objective of our study is to examine whether a two-week intervention with cerebellar anodal tDCS could lessen ataxia severity in SCA3 patients compared to sham stimulation. The secondary objectives are to investigate if a two-week treatment with cerebellar anodal tDCS (1) diminishes various (cerebellar) non-motor symptoms, (2) enhances the ability of SCA3 patients to acquire conditioned responses in a delay eyeblink classical conditioning paradigm, and (3) restores cerebellar brain inhibition pathways compared to sham stimulation. We will (4) also determine if a single session of tDCS has a transient beneficial effect on ataxia severity.

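### The post-hoc rule is tied to main effects of the TIME by TREATMENT ANOVA, but tDCS versus sham is the interaction, which the article never names

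*Protocol article*

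**What the plan says.** The Statistical analysis section lists the tests together: "Where appropriate, we will use either chi-square tests, t-tests, or two-way ANOVAs with TIME as within-subject factor". The TIME factor has a "number of levels depending on the specific outcome measure, ranging from two to five", and the other factor is "TREATMENT as between-subject factor (anodal tDCS versus sham tDCS"). The next step is that "Bonferroni-corrected post-hoc testing is performed to explore significant main effects". No interaction term appears there or elsewhere in the article, and no listed test is assigned to the primary outcome.

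The question to be answered is stated clearly in other places. Under Objectives, the aim is to learn whether the intervention "could lessen ataxia severity in SCA3 patients compared to sham stimulation". The Abstract says: "The primary outcome measure is the absolute change of the SARA score between baseline and T1". Table 2 repeats this endpoint, and the Discussion says that "the focus will be on the immediate post-treatment (T1) versus baseline differences". Table 2 also lists many secondary outcomes measured at several visits up to T4 (12 months).

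**The concern.** In a design with one within-patient and one between-patient factor, a between-arm difference in change is the TIME by TREATMENT interaction. The two main effects answer other questions.

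- **TIME** is the change averaged over active and sham patients. It includes placebo response, practice and, over long follow-up, disease progression. It compares no treatments.
- **TREATMENT** is the arm difference averaged over visits, including the baseline visit, where no effect can exist. Its error term is the variance between patients, and eligibility runs from SARA 3 to 20.
- TREATMENT has only two levels, so pairwise post-hoc tests of that main effect add nothing to its F test. Read literally, what remains to explore is TIME.

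Two things are at stake. A real difference from sham may not trigger follow-up testing, and a change shared by both arms may trigger it. The risk is greatest for the multi-visit outcomes, where the ANOVA is the natural choice and the Discussion wants the time course of any effect.

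**Working it through.** **1. The plan's own power figure.** The article reports 83% for effect size 0.46, α = 0.05 and N = 20. It does not state the metric, the test or the correlation. Taking 0.46 as Cohen's f (f² = 0.2116), noncentral F calculations give:

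| Test assumed | Noncentrality | Power |
|---|---|---|
| Two groups, one measurement | 0.2116 × 20 = 4.23 | 49% |
| Interaction, 2 levels, correlation 0 | 0.2116 × 20 × 2 = 8.46 | 79% |
| Interaction, 2 levels, correlation 0.5 | 8.46 / 0.5 = 16.93 | 97% |
| Interaction, 4 levels, Cohen-type option | 0.2116 × 20 × 3 = 12.70 | 83.4% |
| TREATMENT main effect, 4 levels, correlation 0.25 | 0.2116 × 80 / 1.75 = 9.67 | 83.7% |
| TREATMENT main effect, 5 levels, correlation 0.3 | 0.2116 × 100 / 2.2 = 9.62 | 83.5% |

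Both interaction and main-effect settings come close to 83%. The figure therefore does not show which effect the authors had in mind.

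**2. Inputs for the illustration.** From the article: 10 per arm and two-sided 0.05 (sidedness assumed). Assumed, because the article gives neither: SARA SD 4.9, close to a uniform spread over 3 to 20 (17/√12 = 4.91), and correlation ρ = 0.8 to 0.95 between T0 and T1. The SD of change is SD × √(2(1−ρ)).

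**3. Interaction with two levels.** This is the same test as a two-sample t-test on change. A between-arm difference of 1.378 SDs of change gives noncentrality 1.378 × √5 = 3.08 on 18 df and power 83%, whatever ρ is.

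**4. TREATMENT main effect for that same effect.** The arm difference averaged over T0 and T1 is half the difference in change. The SD of a patient's two-visit mean is SD × √((1+ρ)/2). The standardised difference is therefore 1.378 × √((1−ρ)/(1+ρ)), and the noncentrality is that value times √5.

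| ρ | Standardised difference | Noncentrality | Power, TREATMENT | Power, interaction |
|---|---|---|---|---|
| 0.8 | 0.459 | 1.03 | 16% | 83% |
| 0.9 | 0.316 | 0.71 | 10% | 83% |
| 0.95 | 0.221 | 0.49 | 8% | 83% |

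Lower correlations soften the contrast without removing it. A separate simulation with a difference of 1.40 SDs of change gave 41% at ρ = 0.5 and 24% at ρ = 0.7, against about 84% for the interaction.

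**5. TIME main effect with no tDCS effect.** Both arms improve by 1.5 points at T1. The noncentrality is 1.5 × √20 / (SD of change), on 18 df.

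| ρ | SD of change | Noncentrality | TIME significant | Interaction significant |
|---|---|---|---|---|
| 0.8 | 3.10 | 2.16 | 54% | 5% |
| 0.9 | 2.19 | 3.06 | 83% | 5% |
| 0.95 | 1.55 | 4.33 | 98% | 5% |

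**6. Natural progression.** The Background describes a SARA change of almost three points, "which would nearly equal the progression in SCA3 over two years", or about 1.5 points a year. T1 is day 12, so the expected drift is 1.5 × 12/365 = 0.05 points, and the two-level TIME test stays at about 5%. Over 12 months it matters: in simulations of a five-level analysis (20,000 trials per setting, compound symmetry assumed), progression alone made TIME significant in 47%, 79% and 99% of trials at ρ = 0.8, 0.9 and 0.95. The interaction stayed at 5%.

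**The case against.** The strongest reply is that the clause governs follow-up testing, not the efficacy test. A two-way ANOVA with these factors normally yields the interaction, and nothing in the text says that it will be ignored. For the primary outcome, each patient has one change value, t-tests are permitted, and a t-test on that change equals the 2 × 2 interaction. The study calls itself exploratory. The article does not spell out the post-hoc contrasts, and a fuller document may do so. Finally, a significant TIME effect when both arms change is a correct result for TIME; it misleads only if read as efficacy.

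Most of this stands, and it limits the point. A reader might infer that the primary analysis tests the wrong hypothesis, or that the sponsor intends to claim efficacy from a TIME effect. The documents support neither: the comparison with sham is stated repeatedly, and a valid test of the primary outcome is available under the text. A reader might also infer that progression distorts the T1 comparison; at day 12 it does not.

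The reply does not rescue the clause itself. It states a trigger, and the trigger names the wrong terms, so this is not a detail left to another document. The permitted t-test is not assigned to the primary outcome, and a single t-test on T1 change does not cover the multi-visit outcomes. Exploratory status does not turn a contrast pooled over arms into a comparison with sham.

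**Conclusion.** The clause is wrong as written and should be fixed. It makes follow-up depend on terms that do not isolate tDCS from sham and leaves the relevant term unnamed. The consequence falls mainly on the multi-visit outcomes; for the primary outcome the fault is lack of commitment to a valid test that the text already allows.

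The logical point needs no numbers. The sizes in the working are illustrations that rest on normal data and on an SD and correlations that the article does not give. The power loss on TREATMENT depends on the correlation and not on the SD. The rate of significant TIME effects depends on both, and on an assumed shared improvement of 1.5 points.

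**What to change.** Replace the post-hoc sentence with text such as:

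> The treatment effect is the TIME × TREATMENT interaction. For the primary outcome this is the between-arm difference in SARA change from T0 to T1, with 95% CI. Bonferroni-corrected between-arm contrasts of change from T0 at the other visits follow a significant interaction. Main effects of TIME or TREATMENT, and within-arm changes, are not taken as evidence of efficacy.

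This keeps the only multiplicity correction that the section contains and singles out T1. The cost is a few sentences in the analysis section, with no new data, patients or software.

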
Inspired by these promising findings, we designed the clinically-oriented SCA3-tDCS study to investigate whether cerebellar anodal tDCS, compared to sham stimulation, decreases ataxia severity and a variety of (cerebellar) non-motor symptoms in a homogeneous cohort of SCA3 patients and if so, what the duration of this beneficial effect is.

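### For secondary outcomes followed over T0 and T1–T4, Bonferroni post-hoc testing gives the stated T1 focus no priority and is needlessly conservative for the duration question; planned between-arm contrasts with Holm would serve both better

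*Protocol article*

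**What the plan says.** The Statistical analysis section of the protocol article sets out the methods in general terms: "Where appropriate, we will use either chi-square tests, t-tests, or two-way ANOVAs with TIME as within-subject factor", with TREATMENT (anodal versus sham) as the between-subject factor. The TIME factor has a "number of levels depending on the specific outcome measure, ranging from two to five". The only multiplicity rule follows: "Bonferroni-corrected post-hoc testing is performed to explore significant main effects". No comparison family, contrast or priority among visits is given.

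Tables 1 and 2 show which outcomes reach five levels. INAS, EQ-5D-5L, PHQ-9, POMS, the CCAS scale and FARS part II are measured at exactly T0, T1, T2, T3 and T4. SARA, 8MWT, 9HPT and PATA share those visits and have one more assessment after the first session.

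The aims are stated elsewhere. The Discussion says "While the focus will be on the immediate post-treatment (T1) versus baseline differences, we plan to have a follow-up of up to one year". The Background asks whether there is a benefit and "if so, what the duration of this beneficial effect is". The primary outcome is a single quantity, the SARA change from baseline to T1. The only power statement concerns that outcome: "a power of 83% to detect significant differences when using SARA as the primary outcome measure" ("effect size 0.46, α = 0.05, sample size 20"). The same section calls the study exploratory.

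**The concern.** The protocol's questions come in a natural sequence: is there a difference between arms just after treatment, and if so, how long does it persist? Bonferroni treats all comparisons in its family alike. Applied over five visits, it makes the T1 comparison pay for the visits at 6 and 12 months, although T1 is the declared focus. It also makes each later visit pass the full correction even when earlier visits have already shown an effect, which is where the duration question is settled.

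With 10 patients per arm there is little power to spare. The risk is that a real T1 effect on gait, dexterity, mood or cognition goes undeclared, or that the apparent duration is cut short, because of the adjustment and not the data. Other methods control the same family-wise error at lower cost.

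**Working it through.** **Inputs from the protocol article.** 10 patients per arm; alpha 0.05, taken as two-sided because sidedness is not stated; TIME with up to five levels; stated power 83% with effect size 0.46, for SARA as primary outcome.

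**Assumptions, not in the document.**
- Bonferroni is applied to between-arm differences in change from T0.
- The family is either the four comparisons with baseline, or all pairwise comparisons of five visits: 5 × 4 / 2 = 10.
- The per-test levels are then 0.05/4 = 0.0125 and 0.05/10 = 0.005.

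**The plan's own figure.** For a two-sample t-test with 10 per arm, 0.46 read as d gives 16% power. Read as Cohen's f, so that d = 2 × 0.46 = 0.92, it gives 49%. Neither reproduces 83%. About 83% does arise under settings that the protocol does not state, for example a two-level time-by-treatment interaction with correlation about 0.11, or a between-arm test over five levels with correlation 0.3 (83.5%). The 83% is therefore not shown to be wrong, but it cannot be taken as the power of a T1 t-test. It serves below only as a benchmark.

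**Power of one between-arm contrast.** Noncentral t with df = 2 × 10 − 2 = 18 and noncentrality d × √(10/2).
- d = 1.378 is the value that gives 83% at 0.05; noncentrality 1.378 × 2.236 = 3.08.
- d = 0.92 has noncentrality 0.92 × 2.236 = 2.06.

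| Level | Critical t (18 df) | Power, d = 1.378 | Power, d = 0.92 |
|---|---|---|---|
| 0.05 | 2.10 | 83.0% | 49.5% |
| 0.0125 (4 contrasts) | 2.77 | 62.4% | 26.9% |
| 0.005 (10 contrasts) | 3.20 | 47.6% | 16.7% |

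The cost is 83.0 − 62.4 = 20.6 to 83.0 − 47.6 = 35.4 points at the larger effect, and 49.5 − 26.9 = 22.6 to 49.5 − 16.7 = 32.8 points at the smaller. No ANOVA gate is modelled. Requiring a significant omnibus test as well could only lower these figures.

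**Holm on the same four contrasts.** Holm compares the ordered p-values with 0.05/4, 0.05/3, 0.05/2 and 0.05, and stops at the first failure. It rejects whatever Bonferroni rejects and sometimes more, with the same family-wise error control. Simulation used 20,000 trials per scenario, 10 versus 10, visits at 0, 0.4, 3, 6 and 12 months, reliability 0.9, monthly correlation decay of 1.00, 0.99 or 0.97, and d standardised at each visit:
- d = 1.378 at all four visits: T1 power rises from about 62% to 73%, and the chance of showing all four visits from about 30% to 56%.
- d = 1.378 at T1 and T2 only: T1 power goes from about 62% to 65%.
- d = 1.378 at T1 only: virtually no gain (62.6% with Bonferroni, 62.7% with Holm).
- No effect at any visit: family-wise error of Holm 4.1–4.7%.

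**Fixed order T1, T2, T3, T4, each at 0.05.** T1 keeps 83% at d = 1.378, and simulated family-wise error is about 5%. If effects appear only at T2–T4 with d = 1.378, T2 is formally declared in about 4% of trials, against about 63% with Bonferroni over four.

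**The case against.** The strongest objections are these.

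- **The 83% belongs to another test.** It is stated for the SARA primary outcome, a single contrast that the section allows to be tested by a t-test or a two-level ANOVA with nothing to correct. A reader might infer that the trial's primary power falls from 83% to 48–62%. The documents do not support that, and no power is stated for the outcomes at issue. This objection stands, and 83% is used here only as a benchmark.
- **The corrected comparisons may not be between arms.** TREATMENT has two levels, so Bonferroni on main effects can act only over TIME, with the arms pooled. The power figures describe the between-arm contrast that the objectives need, which is not literally the one the sentence corrects. This stands, and the figures are conditional on it.
- **The family is not stated, and t-tests are also allowed.** Families of four and ten are assumptions. It would also be too strong to say that visit-specific effects can be reached only through the post-hoc step. Both points stand.
- **Bonferroni is valid and the study is exploratory.** It is valid: there is no inflated error here. The exploratory label does not justify a stricter rule than error control needs, and with 10 per arm it makes the loss harder to afford.
- **Real T1 effects are not bound to be missed.** At d = 1.38 with four contrasts, detection is still more likely than not (62%). At d = 0.92, power is only 49% with no correction, so sample size is already the main limit. This stands.

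**Conclusion.** The point holds for secondary outcomes analysed over T0 and T1–T4. As written, the rule gives the declared T1 focus no priority and is more conservative than necessary for the duration question. If it is applied to between-arm contrasts with 10 per arm and two-sided tests, the T1 contrast loses about 21 points of power with four contrasts and 35 with ten at d = 1.38, and about 23 and 33 points at d = 0.92. These sizes rest on assumed families and effects; the protocol fixes neither.

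The primary SARA T1 contrast need not be affected, and Bonferroni is not an error in itself. The weakness is an inefficient choice that fits the protocol's own questions poorly. A reader might also conclude that a fixed testing order is required. It is not: its advantage for T1 is bought by giving up formal detection of effects that first appear later, in a study that treats the time curve as important.

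**What to change.** For each outcome followed over T1–T4, replace the Bonferroni post-hoc step with four planned contrasts: the tDCS-minus-sham difference in change from T0 at T1, T2, T3 and T4. Adjust these four by Holm at two-sided 0.05, and report every visit's estimate with a 95% CI whether or not it is significant. State that the primary SARA contrast at T1 is a single planned test outside this adjustment.

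The cost is a sentence or two in the analysis section, with no new patients, visits or data. Against Bonferroni on the same four contrasts, Holm gives up neither power nor error control, but it should not be presented as restoring full T1 power, since it gains almost nothing when only T1 has an effect. If the sponsor values T1 above everything else, a fixed T1-to-T4 order is an option. The plan should then say that an effect first appearing after T1 will be described but not formally tested.
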